## 2. Materials and Methods

### 2.1. Study Design

The proposed study is a prospective double-blind RCT with two arms. A CONSORT flow chart for enrollment and randomization is shown in Figure 1. Patients fulfilling inclusion criteria, once they have signed the informed consent form, will undergo a baseline assessment (T0) using the below-listed tests and will be randomized to one of two groups: experimental and control. Both groups will be exposed to three VR sessions each lasting approximately 20 min during a one-week period. The first session will be carried out immediately after enrollment and T0, whereas the next two will be carried out in the following days when the patients will report to have a migraine attack. At T0 and at the end of the intervention (T1), the patients will fill in a questionnaire based on behavioral measures related to their emotional and psychological state and their body image perception. T1 assessment will then be carried out at the end of the last VR session. Before and after each VR session the level of pain, body image, and affective state of the patients will be assessed. Furthermore, after each VR session, the sense of embodiment (experimental group) or the sense of immersiveness (control group) will be assessed.

This study protocol conforms to the Standard Protocol Items: Recommendations for Interventional Trials (SPIRIT) guidelines (see Supplementary Table S1).

### 2.2. Study Setting

This trial will take place at the Headache Science and Neurorehabilitation Center of the IRCCS National Neurological Institute Mondino Foundation (Pavia), a tertiary referral center for the diagnosis and care of migraine in Northern Italy.

### 2.3. Participant Recruitment and Eligibility Criteria

Participants will be recruited among patients referred to the Center. An expert neurologist will verify the eligibility criteria during the recruitment process based on the participants’ history, headache diaries, and neurological evaluation.

Inclusion criteria for patients will be: (a) 18–65 years of age; (b) female sex; (c) fulfilment of the ICHD-3 criteria [2] for CM (with or without medication overuse); (d) previous history of migraine as primary headache; (e) an intensity of migraine attacks between 20 and 80 on a 0–100 VAS. Only females will be included in this study because of the reported differences on pain perception between males and females [70].

Exclusion criteria will be: (a) epilepsy, psychosis, intellectual disability, pregnant women and breastfeeding women; (b) visual problems; (c) presence of chronic non-cephalic pain.

All patients will receive the advice to avoid any abortive medication during the study period. Preventive treatments will be allowed given that they are not expected to affect the outcome of this study.

In order to achieve adequate participant enrolment to reach the target sample size (see Section 2.12.1), we will provide notice of this study among patients referred to our clinic as well as in local newspapers.

### 2.4. Participant Evaluation

All patients will undergo the following assessment measures, as reported in Table 1, performed by a psychologist, who will be also be responsible for obtaining the informed consent form.

At T0 and T1, the participants will fill in a series of psychological questionnaires as with regards their affective and emotional state:(a)Body Satisfaction Scale (BSS) [71] designed to measure satisfaction/dissatisfaction with 16 body parts;(b)Hospital Anxiety and Depression Scale (HADS) [72] for anxious and depressive symptomatology;(c)Emotive Regulation Questionnaire (ERQ) [73], which is a self-report measure of two emotion regulation strategies (i.e., cognitive reappraisal and expressive suppression);(d)Difficulties in Emotion Regulation Scale (DERS) [74] measuring emotion regulation problems.

Moreover, within each of the three sessions, they will be also evaluated before and after the visual exposure (six times) with the following measures:(a)Pain Visual Analogue Scale (VAS) for pain level on a 0 to 100 scale;(b)Body Image Questionnaire (BIQ) [75] for body image perception;(c)Positive and Negative Affect Schedule (PANAS) [76] for the positive and negative affective state.

Finally, after each visual exposure session, for a total of three times, the patients of the experimental group will fill in a questionnaire (i.e., embodiment questionnaire) related to the level of sense of belonging to the virtual body and the experience of illusion of enfacement [77]. The control group will fill in a questionnaire (i.e., immersive questionnaire) assessing the level of immersion in the virtual environment [39]. This is in order to assess the subjective strength of the two conditions to which patients will be exposed.

### 2.5. Randomization, Stratification, and Allocation

After T0, random numbers will be generated from a uniform distribution in the range 0–1, dividing the range in two equal intervals and assigning each patient to the group corresponding to the sampled number (1:1 ratio). Allocation of participants will be performed by an independent data manager, who will be not involved in the data collection/analysis.

### 2.6. Blinding

This is a double blinded study: both the patients and the clinicians collecting the data will be blinded to the group allocation. The participants do not know to what kind of VR conditions they will be exposed. On the ethics consent form, they are informed that they will be exposed in a random fashion to one of two VR conditions consisting in the exposure to a virtual environment through a head-mounted display (HMD). The clinicians coding the data are not aware of the group allocation.

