### 2.8. Visual-Exposure Conditions

Each VR session will be conducted by the same experimenter (i.e., a psychologist) in order to avoid any related effects. Both visual exposure conditions will be conducted with the participant seated in a chair. In case of cyber sickness, participants will be free to discontinue the VR exposure at any moment.

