#### 2.8.1. Experimental Group

Patients in the experimental group will be exposed to the enfacement illusion condition, conducted similarly to other studies in other fields of research [47] (Figure 3 and Figure 4). In detail, patients will see, through the HMD, a virtual body sitting in front of them in the same position showing a happy face expression. Each session will consist of four phases:(1)Observation of the virtual facial expression and habituation to the virtual environment: the experimenter will ask patients to focus their attention on the face of the virtual body sitting in front of them for about one minute.(2)Visuo–tactile stimulation: in order to induce the enfacement illusion in the patients, the experimenter will use a brush to apply synchronous visuo–tactile stimulation to the real face of the patients, while they will be observing a synchronous tactile stimulation on the happy face displayed in the 360° video equally applied by the experimenter in the same place and at the same time. The synchronous visuo–tactile stimulation will be applied for 2 min.(3)The observation of the virtual facial expression and habituation to the virtual environment phase will be repeated to update habituation to the virtual environment.(4)The synchronous visuo–tactile stimulation phase will be repeated to update the induction of the enfacement illusion.

Overall, the patients will receive 4 min of synchronous visuo–tactile stimulation to induce the enfacement illusion to the happy face displayed in the 360° video through the HMD. The synchronous stimulation will be recorded with a metronome sound (60 beats per minute) in the 360° video. During the experimental session, the researcher will stimulate the face of the patients which at the same time will be synchronized with the beat sound displayed in the video. Patients will observe the same situation when they are immersed into the 360° virtual scenario: a researcher stimulating the virtual face placed in front of them. A beep sound will indicate the experimenter wants to start the stimulation, and he/she will follow the sound of the metronome for each stimulation. After exposure to the 360° video, the patients will fill in a questionnaire regarding the induction of the ‘enfacement illusion’ adapted from [77].

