### 2.10. Data Collection

Psychologists conducting evaluations will receive appropriate instruction and guidance regarding all of the outcome parameters and assessments that will be taken. The research staff collecting the data will be blinded to the group allocation.

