### 2.13. Ethical Issues and Dissemination Plan

This trial will involve human participants, VR-based systems, data collection, elaboration, and abstraction used for the evaluation of the two VR options. This study has been approved by the local ethics committee (IRCCS San Matteo Hospital, Pavia) and will be conducted in accordance with the Declaration of Helsinki and reported according to CONSORT guidelines [78,79]. Any subsequent modification to the protocol which may impact the study (e.g., objectives, study population, sample sizes, procedures) will be submitted as an amendment and reviewed by the IRCCS San Matteo Hospital ethics committee for approval. In addition to ethical approval, all the procedures and the data managed have been approved by the data protection officer of the IRCCS Mondino Foundation who guarantees the study’s compliance to the GDPR (General Data Protection Regulation). The information provided when presenting the informed consent form to the participants will be given in a language appropriate to the individuals’ level of understanding. In particular, in the consent form, participants are informed that they will receive, in a random fashion, one of two VR conditions consisting of exposure to a virtual environment through an HMD. We do not provide additional information about the content of each VR exposure in order to avoid influencing the subjective strength of the virtual reality experience, as assessed by the embodiment and immersive questionnaires. Participants will be encouraged to ask questions before signing the informed consent form and they will be free to discontinue the study at any moment. In order to improve the adherence to the protocol, the experimenter responsible for collecting the informed consent forms will highlight to the patients the opportunity to take part in this study as a way to improve the knowledge of their disease as well as to provide complementary non-pharmacological approaches in the future. Due to the low risk associated with study participation, an annual audit of the study, the Data Monitoring Committee (DMC), and interim analyses are not required. Additionally, a data safety monitoring board is not required because we are not investigating a medical product and we do not foresee any major risks associated with study participation.

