**Figure 6 jcm-11-06876-f006:**
[figure not shown]
Caption of the pleasant virtual environment retrieved from the Calm Place app.

**Table 1 jcm-11-06876-t001:** Materials for participant evaluation as a function of the testing session.

		Session 1		Session 2		Session 3		
Outcome Measures	T0	Pre	Post	Pre	Post	Pre	Post	T1
Primary outcome								
Pain Visual Analogue Scale (VAS)		x	x	x	x	x	x	
Secondary outcome								
Hospital Anxiety and Depression Scale (HADS)	x							x
Emotive Regulation Questionnaire (ERQ)	x							x
Difficulties in Emotion Regulation Scale (DERS	x							x
Body Satisfaction Scale (BSS)	x							x
Body Image Questionnaire (BIQ)		x	x	x	x	x	x	
Positive and Negative Affect Schedule (PANAS)		x	x	x	x	x	x	
Embodiment/Immersive questionnaire			x		x		x	

Note: the embodiment questionnaire is administered to the experimental group, whereas the immersive questionnaire is administered to the control group.

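### The trial is called double-blind, but the session operator knows the arm, patients know their own condition, and the article describes no blinded collector of the primary pain score

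*Protocol article*

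**What the plan says.** The Abstract and Section 2.1 describe a double-blind trial. Section 2.6 defines this: "both the patients and the clinicians collecting the data will be blinded to the group allocation". It adds that coders do not know the allocation. Section 2.10 repeats the claim for collection: "The research staff collecting the data will be blinded to the group allocation".

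Other sections describe who does what:

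- **Assessment (2.4).** The Table 1 measures, which include the pain VAS, are "performed by a psychologist, who will be also be responsible for obtaining the informed consent form".
- **VAS session delivery (2.8).** "Each VR session will be conducted by the same experimenter (i.e., a psychologist) in order to avoid any related effects".
- **Experimental arm (2.8.1).** "the experimenter will use a brush to apply synchronous visuo–tactile stimulation to the real face of the patients".
- **Control arm (2.8.2).** The experimenter asks patients to say what they see. No brushing is described.
- **Consent (2.13).** The person taking consent is "the experimenter responsible for collecting the informed consent forms".
- **Forms (Table 1 note).** "the embodiment questionnaire is administered to the experimental group, whereas the immersive questionnaire is administered to the control group". Table 1 places this form in the same Post columns as the VAS, BIQ and PANAS.

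Sections 2.6 and 2.13 say that patients are told only that they will receive one of two VR conditions, with the content of each withheld.

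**The concern.** The primary outcome is a self-rated 0–100 pain score. Strengths and Limitations says it is given directly after the exposure, so it follows close contact with whoever ran the session. If that person knows the arm and also collects the score, tone, prompting or timing can differ between arms. Neither the intention-to-treat approach nor the mixed models in Section 2.12.2 can remove such a difference.

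A reader who sees the double-blind label will take this source of bias as controlled. The label is therefore a claim about the credibility of the primary result, and it should match the procedures.

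**Working it through.** **Step 1. Compare the claim with the procedures, role by role.**

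| Role | Claimed | What the procedures imply |
|---|---|---|
| Session operator | Not named separately in 2.6 | Knows the arm: brushes the face (2.8.1) or asks for a description of the scene (2.8.2) |
| Collector of the VAS | Blinded (2.6, 2.10) | Appears to be the operator. No separate blinded assessor is described |
| Anyone handling both the VAS and the arm-specific form | Blinded, if a data collector | Learns the arm from the form (2.4, Table 1) |
| Patient | Blinded (2.6) | Knows own condition. Masked to the other condition and, presumably, the hypothesis |
| Data coder | Blinded (2.6) | Can be true |

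**Step 2. Is the operator also the assessor?** Section 2.4 has one psychologist who assesses and takes consent. Section 2.13 calls the consent-taker the experimenter. Section 2.8 says the experimenter, a psychologist, runs every session. The chain runs assessor = consent-taker = experimenter = operator. It is an inference across three sections, and Section 2.10 speaks of psychologists in the plural.

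**Step 3. Which primary data are exposed?** Section 2.12.2 compares the groups on the VAS at session 1 pre and session 3 post. The first may precede any unblinding. The second follows three exposures and the arm-specific forms of sessions 1 and 2.

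**Step 4. Reproduce the planned sample size, to fix n for the illustration.** Section 2.12.1 gives changes of −40 and 10, SD 100, one-tailed alpha 0.05 and 80% power.

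- d = |−40 − 10| / 100 = 0.5
- n per group = 2 × (1.645 + 0.842)² / 0.5² = 49.5, so 50. The stated 50 per group reproduces. The exact t calculation gives 50.15.

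**Step 5. Illustrate the effect of a bias.** The documents give no size for it, so a range is assumed. With no true effect and a reporting bias of b SD, the t statistic is noncentral with df = 98 and noncentrality λ = b × √(50/2) = 5b. The planned ANOVA with two groups is a two-sided test, with critical value 1.984.

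| Assumed bias b (SD) | λ | Two-sided false-positive rate |
|---|---|---|
| 0.05 | 0.25 | 5.7% |
| 0.1 | 0.5 | 7.9% |
| 0.2 | 1.0 | 16.8% |
| 0.3 | 1.5 | 31.8% |

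As a guide to scale, a shift of 5 VAS points is 5/100 = 0.05 SD with the SD stated in Section 2.12.1, and 5/25 = 0.2 SD if the SD of change were 25. Both the 5 points and the SD of 25 are assumptions.

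**The case against.** The strongest reply is that the article does not rule out an arrangement in which its claims largely hold. Much of this stands, and it limits the point in four ways.

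- **One person in both roles.** A reader might infer that the article states this. It does not. The nouns in Sections 2.4 and 2.8 are indefinite, Section 2.10 has a plural, and the article uses experimenter and researcher loosely. Overlap is the natural reading, but not a stated fact.
- **Any assessor must be unblinded.** A reader might infer this from the shared Post columns. Table 1 does not show the order of the forms or who hands them out. Someone who collects only the VAS and never sees the arm-specific form could remain blind. The article describes no such person.
- **Patient expectation favours the experimental arm.** A reader might infer this too. The documents do not support it: the content of both conditions is withheld, and the Introduction presents the control as a pleasant environment already known to distract from pain. Operator influence has a more plausible direction, given the directional hypothesis, but no evidence on it is given.
- **A single inflated error rate.** Quoting only the 0.2 SD result, or a one-tailed rate, would overstate what is known. No bias size is documented, and the analysis in Section 2.12.2 is not directional.

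It is also fair that nobody could blind the person doing the brushing, and that Strengths and Limitations calls this a pilot study. Neither makes the blinding statement accurate. The plan can describe its masking correctly without blinding the operator.

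**Conclusion.** The point holds as a mismatch between the stated blinding and the described procedures. It is certain that the operator knows the arm and that patients know their own condition. It is likely, but inferred, that the operator also collects the VAS. Blinding of coders is not in doubt.

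The consequence cannot be sized from the documents. On the assumed range of 0.05 to 0.3 SD, with 50 per group, no true effect and a two-sided 5% test, the false-positive rate runs from about 6% to about 32%. The lower end is close to negligible and the upper end is serious, so the plan should limit the opportunity for bias and not rely on the label. This needs settling before data collection, because prompting and form order cannot be corrected afterwards.

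**What to change.** 1. In Sections 2.6 and 2.10, state who delivers the sessions, who collects the VAS and who hands out the arm-specific questionnaire.
2. Replace the double-blind label, there and in the Abstract and Section 2.1, with the roles actually masked: patients unaware of the other condition and of the hypothesis, operator not blinded, coder and analyst blinded by neutral arm codes.
3. At each post-session assessment, have the patient self-complete the VAS, BIQ and PANAS from a fixed script, without prompting by the operator, before the arm-specific questionnaire is shown.
4. File the arm-specific questionnaire separately from the outcome forms.

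The cost is the loss of the double-blind label, some rewording, and a fixed order for forms already in use. No extra staff are needed. Operator influence during the session itself would remain and should be acknowledged as a limitation.

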### 2.7. Apparatus

We will use an HMD (Oculus Quest2 created by Facebook Technologies, a division of Meta, Facebook Inc., Menlo Park, CA, USA —see Figure 2), with a resolution of 1832 × 1920 pixels per eye resolution at 120 Hz to show the 360° video in the experimental group, which will be displayed through a VR video player app (Skybox VR player for Oculus, v. 1.0.0, Skybox Studio, Vancouver, BC, Canada), or the virtual environment displayed through the Calm Place app (v. 0.3.1) (Calm Inc., San Francisco, CA, USA) in the control group.

### 2.8. Visual-Exposure Conditions

Each VR session will be conducted by the same experimenter (i.e., a psychologist) in order to avoid any related effects. Both visual exposure conditions will be conducted with the participant seated in a chair. In case of cyber sickness, participants will be free to discontinue the VR exposure at any moment.

#### 2.8.1. Experimental Group

Patients in the experimental group will be exposed to the enfacement illusion condition, conducted similarly to other studies in other fields of research [47] (Figure 3 and Figure 4). In detail, patients will see, through the HMD, a virtual body sitting in front of them in the same position showing a happy face expression. Each session will consist of four phases:(1)Observation of the virtual facial expression and habituation to the virtual environment: the experimenter will ask patients to focus their attention on the face of the virtual body sitting in front of them for about one minute.(2)Visuo–tactile stimulation: in order to induce the enfacement illusion in the patients, the experimenter will use a brush to apply synchronous visuo–tactile stimulation to the real face of the patients, while they will be observing a synchronous tactile stimulation on the happy face displayed in the 360° video equally applied by the experimenter in the same place and at the same time. The synchronous visuo–tactile stimulation will be applied for 2 min.(3)The observation of the virtual facial expression and habituation to the virtual environment phase will be repeated to update habituation to the virtual environment.(4)The synchronous visuo–tactile stimulation phase will be repeated to update the induction of the enfacement illusion.

Overall, the patients will receive 4 min of synchronous visuo–tactile stimulation to induce the enfacement illusion to the happy face displayed in the 360° video through the HMD. The synchronous stimulation will be recorded with a metronome sound (60 beats per minute) in the 360° video. During the experimental session, the researcher will stimulate the face of the patients which at the same time will be synchronized with the beat sound displayed in the video. Patients will observe the same situation when they are immersed into the 360° virtual scenario: a researcher stimulating the virtual face placed in front of them. A beep sound will indicate the experimenter wants to start the stimulation, and he/she will follow the sound of the metronome for each stimulation. After exposure to the 360° video, the patients will fill in a questionnaire regarding the induction of the ‘enfacement illusion’ adapted from [77].

#### 2.8.2. Control Group

Participants in the control group will be exposed to a visual stimulation by observing a pleasant immersive virtual reality environment [69] (Figure 5 and Figure 6). As in the experimental group, there will be two minutes for the habituation to the virtual environment, where the experimenter will ask the patients to describe what they see. Then, the patients will observe the pleasant virtual environment for about 4 min.

After immersion into the virtual environment, the patients will fill in a questionnaire regarding the virtual reality experience adapted from [39].

